#### Relapse treatment

We recommend to treat relapses during the study with corticosteroids in form of intravenous methylprednisolone at a dose of 500mg daily for 5 consecutive days i.v. with or without tapering-out. The decision to treat an exacerbation is at the discretion of the treating physician.

### Drug accountability

Drug accountability will be maintained at the research site.

The investigator will keep a record of the investigational product (Atorvastatin) dispensed. The investigational product must be stored in a locked storage facility and protected from unauthorized access.

Patients must return used or unused investigational product in the original packages upon termination of the study at the latest.

# Efficacy and Safety Variables

## Efficacy variables

The objectives of this study are to assess the efficacy, safety and tolerability of the combination of Atorvastatin 40 mg p.o. daily and Interferon-beta-1b sc e.o.d compared to monotherapy with Interferon-beta-1b sc e.o.d in patients with multiple sclerosis.

### Primary efficacy variables

The primary endpoint of the study is to determine the efficacy of Atorvastatin as add-on therapy to a basic treatment with Interferon-beta-1b evaluating the disease activity measured by the proportion of patients with new T2 lesions after 12 months of treatment.

### Secondary efficacy variables

The following points will be analyzed comparing group one and two.

- Gd-enhancing lesion on T1-weighted images after 12 months of treatment.
- Change of total T2 hyperintense lesion volume (burden of disease, BOD)
- Clinical disease progression (EDSS, MSFC)
- Functional systems subscores (of EDSS and MSFC)
- Number of patients relapse-free after 12 months of treatment
- Relapse rate after 12 months of treatment
- Cortical atrophy (changes in brain volume, changes in grey matter and white matter) after 12 months of treatment
- Sieric levels of anti-MOG- and anti-MBP-antibodies
- Sierial levels of neutralizing Antibodies (Nab)

## Safety variables

### Safety and Tolerability definition

Safety and tolerability will be measured by reporting of adverse events, safety laboratory measurements and drop out rate due to adverse events.

### Laboratory measurements

#### Serum Chemistry

Sodium, Potassium, Chloride, Calcium, Urea-N, Creatinine, ASAT (SGOT), ALAT (SGPT), GGT, alkaline phospatase, Uric Acid, total and direct bilirubin, total protein and albumin, Glucose

#### Serum lipid profile

Triglycerides, total cholesterol, free cholesterol, HDL, LDL

#### Hematology

RBC, WBC, Differential count, Platelet Count, Hemoglobin (Hb), Hematocrit, absolute lymphocyte count

#### Pregnancy Test in Women

Serum beta-HCG

#### Creatine phosphokinase (CPK)

Total CPK, isoenzymes only if total CPK is more than twice the normal upper range.

#### Immunology:

Neutralizing antibodies (Nab), anti-MOG- and anti-MBP-Antibodies

#### Thyroid Profile

TSH

## Assessment of patient characteristics

### Demographic data

Documentation of date of birth, sex, and ethnic group

### Vital signs

Height, weight, temperature, heart rate (for 1 min, after being seated for 3 min), and systolic and diastolic blood pressure (after being seated for 3 min) will be measured. In case of clinically significant deviations, the measurements will be repeated before documentation.

### Neurological examination

Will be performed by the Evaluating Physician. The results of the standardized neurological examination and Kurtzke EDSS score and MFSC will be recorded.

### Medical and surgical history

The treating physician will ask about relevant diseases of the following organs/systems: skin, eyes, ears, nose, and throat, head and neck (including the thyroid), lungs, heart, breasts, liver, gastro-intestinal system, lymph nodes, musculoskeletal system (including extremities and spine), genito-urinary system. History of allergies will be queried, as well as other abnormalities (if indicated). Furthermore, patients will also be asked if they have a history of alcohol or drug abuse, and a history of psychiatric disorder, with particular regard to known depression or suicidal tendencies. Any previous disease or surgery reported will also be documented.

The contraceptive method used will be recorded, and if applicable, the age at menopause. Patients of childbearing potential will be instructed to discontinue study medication if they become pregnant and immediately notify the Treating Physician.

### MS history:

Date of onset and diagnosis of MS, symptoms, recovery, number of relapses during the past two years

### Medication history

The generic names of the preparations should be recorded and for compound preparations, the trade name should be recorded. For each medication, the indication, dose, unit, frequency, route of administration, and dates of first and last administration will be documented.

### Physical examination

The physical examination will be performed by the Treating Physician. Any abnormal physical examination findings or ongoing symptoms or diseases (except neurological findings related to multiple sclerosis) observed are to be reported. The date when the symptoms first occurred, and the stop date, if appropriate, will be documented.

### ECG

A 12-lead ECG will be performed.

## Magnetic resonance imaging (MRI)

All patients will undergo MRI examination at the time of study entry and at month 12. The study scans should be performed within 14 days of the scheduled visit. If a patient receives a high dose of corticosteroids to treat an exacerbation, then the MRI scan will be postponed until 30 days after the treatment is completed. MRI scans are to be performed following standardized MRI guidelines (see detailed protocol) and will include pre and post contrast,T1 images and T2 images. The MRI scans will be analyzed centrally in a blinded fashion at the MRI core lab. MRI is used in this study as a parameter of activity. Recent studies have shown that the number of T2 positive areas and the number of new lesions on the T2-weighted images considered correlates with the activity detected by MRI with gadolinium, and shows a positive trend in the progression of the disease. Furthermore, new T2 lesions reflect disease activity over the whole interval of 3 months, whereas gadolinium-enhancing lesions reflect only the previous month. A highly concentrated contrast agent will be used for the T1 sequences, to evaluate disease activity of the last month by means of gadolinium-enhancing lesions. T1-weighted sequences of MRI scans will be performed with high concentrated gadobutrol. The contrast medium may occasionally cause nausea and vomiting, it may cause warmth and pain at the injection site. Allergic reactions occur very rarely (anaphylactic shock in 13 of 5 million applications, based on post-marketing surveillance) and in extremely rare instances can be potentially serious.

## Adverse events

An **AE** is defined as any untoward medical occurrence in a patient or clinical investigation subject (volunteer) administered an investigational medicinal product and which does not necessarily have a causal relationship with this treatment. An AE can therefore be any unfavorable and unintended sign (including an abnormal but clinical significant laboratory finding), symptom, or disease temporally associated with the use of a medicinal (investigational) product, whether or not the AE is considered related to the medicinal (investigational) product. AEs are to be coded using an internationally recognized dictionary.

### Documentation

The patient should be closely observed by the investigator. In case of drug-related AE (i.e.,‘possible’, ‘probable’ or ‘definite’ drug relationship assessment), the investigator is urged to monitor the patient and document the outcome on a separate form (additional CRF page)*.*

Any AEs (observed, volunteered, or elicited) are to be documented in detail indicated on the CRF.

The following information is required:

- The **date of onset** of any AEs
- The fact whether an AE is considered to be serious (**SAE** no/yes)
- The maximum **intensity** (mild, moderate or severe; for definitions, see below)
- The main **pattern** (for definitions, see below)
- **Study drug action** because of this AE (drug withdrawn, dose not changed, etc.)
- **Details** of AE-related study drug actions (free text), if applicable
- Specific **treatment** of the AE (no/yes)
- The **study drug relationship** of the AE to the investigational product (for definitions, see below)
- The **outcome** of the adverse event (recovered, recovering, not recovered, recovered with residual effects, fatal, unknown)
- **Date ended** (if recovered)
- An assessment of the **seriousness** of the event will be made by the investigator, who is to complete a special form provided by the sponsor in the case of a serious adverse event (SAE). However, SAEs will also be recorded briefly on the "Adverse Event Form" of the CRF. A definition of serious adverse events is provided below.

### Categories/Definition

**Every study drug administration**:

Events that occur in a clear time relationship to every study drug administration

**Intermittent:**

Regular or irregular repeating events that are clearly of the same kind and same cause, but not clearly time related to study drug administration

**Continuous**:

Events that are continuously present within the whole time period which is covered by the form, but not clearly time related to study drug administration

**Other**:

All other pattern, need to be specified in the following text field

### Intensity

The investigator is to classify the intensity of an **AE** according to the following definitions:

**Mild**: The intensity of the event is assessed as mild, taking into account the possible range of the intensity of the event.

**Moderate:** The intensity of the event is assessed as moderate, taking into account the possible range of the intensity of the event.

**Severe:** The intensity of the event is assessed as severe, taking into account the possible range of the intensity of the event.

### Drug relationship

The investigator has to classify the drug relationship of an AE according to the following definitions:

| **Categories** | Definition |
| --- | --- |
| None | The time course between administration of the study drug and occurrence or worsening of the AE is out a causal relationship and/or another cause is confirmed and no indication of involvement of the study drug in the occurrence/worsening of the AE exists. |
| **Unlikely** | The time course between administration of the study drug and occurrence or worsening of the AE makes a causal relationship unlikely and/or the known effects of the study drug or of the substance class provide no indication of involvement in occurrence/worsening of the AE and another cause adequately explaining the AE is known and/or regarding the occurrence/worsening of the AE a plausible causal chain may be deduced from the known effects of the study drug or the substance class, but another cause is much more probable and/or another cause is confirmed and involvement of the study drug in the occurrence/worsening of the adverse event is unlikely. |
| **Possible** | Regarding the occurrence/worsening of the AE, a plausible causal chain may be deduced from the pharmacological properties of the study drug or the substance class, but another cause just as likely to be involved is also known or although the pharmacological properties of the study drug or the substance class provide no indication of involvement in the occurrence/worsening of the AE, no other cause gives adequate explanation |
| **Probable** | The pharmacological properties of the study drug or of the substance class and/or the course of the AE after dechallenge and, if applicable, after rechallenge and/or specific tests (e.g. positive allergy test, antibodies against study drug/metabolites) suggest involvement of the study drug in the occurrence/worsening of the AE, although another cause cannot be ruled out. |
| **Definite** | The pharmacological properties of the study drug or of the substance class and the course of the AE after dechallenge and, if applicable, after rechallenge and specific tests (e.g. positive allergy test, antibodies against study drug/metabolites) indicate involvement of the study drug in the occurrence/worsening of the AE and no indication of other causes exists. |

### Serious adverse events

The following SAE definition is based on ICH guidelines and the final rule issued by the Food and Drug Administration (FDA) and effective 6 Apr 1998.

A **SAE** is classified as any untoward medical occurrence that at any dose

- results in death, or
- is life-threatening, or
- requires inpatient hospitalization (except pre-planned hospitalization and **hospitalisation due to relapse or other medical problems of multiple sclerosis**) or prolongation of existing hospitalization, or
- results in persistent or significant disability/incapacity, or
- involves malignancy or is a congenital anomaly / birth defect

Medical and scientific judgment should be exercised in deciding whether expedited reporting is appropriate in other situations, such as important medical events that may not be immediately life-threatening or result in death or hospitalization but may jeopardize the volunteer or may require intervention to prevent one of the other outcomes listed in the definition above. These should also usually be considered serious. Examples of such events are intensive treatment in an emergency room or at home for allergic bronchospasm; blood dyscrasias or convulsions that do not result in hospitalization; or development of drug dependency or drug abuse.

The investigator should take appropriate diagnostic and therapeutic measures to minimize the risk to the patient. Where appropriate he / she should take diagnostic measures to collect evidence for clarification of the relationship between the SAE and the investigational product.

The investigator must submit a complete SAE report for all SAEs, regardless of a possible causal relationship, to the primary contact person at the **CRO** **immediately** (at the latest within 24 hours of having gained knowledge of the event).

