### Blinding

This is a rater-blinded study. All patients and the treating physician will be aware whether Atorvastatin is added to the Interferon-beta-1b therapy or not.

Treatment will be administered by the “treating physician” (TP). He/she will acknowledge the treatment administered, he/she will be responsible for patient eligibility, for treatment of adverse events, and for safety examinations.

”Examining physicians” (EP) will be responsible for disability scoring (EDSS, MSFC). They will not be informed whether patients are receiving Atorvastatin or not. Results of scoring will be recorded in a separate sheet. The EP will not acknowledge the treatment groups. Safety issues and other questions should not be discussed between TP and EP. Patients and TP should be informed not to discuss any safety questions with the EP.

In addition, the MRI evaluations will be performed with readers blinded to the treatment group.

Unblinding of the evaluating physician or his/her staff should generally be avoided. Single case unblinding is allowed when the actual treatment must be revealed in order to influence urgent medical care.

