### Expected adverse reactions

**Atorvastatin** is generally well-tolerated and side effects are rare. Minor side effects include constipation, [diarrhea](http://www.medicinenet.com/script/main/art.asp?ArticleKey=1900), fatigue, gas, pruritus, heartburn, and headache. Major side effects include [abdominal pain](http://www.medicinenet.com/script/main/art.asp?ArticleKey=1908) or cramps, blurred vision, [dizziness](http://www.medicinenet.com/script/main/art.asp?ArticleKey=8004), easy bruising or bleeding, itching, muscle pain or cramps, rash, and yellowing of the skin or eyes. [An](javascript:defwindow('An')) [apparent](javascript:defwindow('apparent')) hypersensitivity [syndrome](javascript:defwindow('syndrome')) has been reported rarely. Atorvastatin, like other inhibitors of HMG-CoA reductase, occasionally causes [myopathy](javascript:defwindow('myopathy')) manifested as [muscle](javascript:defwindow('muscle')) pain, [tenderness](javascript:defwindow('tenderness')) or [weakness](javascript:defwindow('weakness')). Myopathy sometimes takes the [form](javascript:defwindow('form')) of [rhabdomyolysis](javascript:defwindow('rhabdomyolysis')) with or without [acute](javascript:defwindow('acute')) [renal](javascript:defwindow('renal')) [failure](javascript:defwindow('failure')) [secondary](javascript:defwindow('secondary')) to myoglobinuria. The [risk](javascript:defwindow('risk')) of [myopathy](javascript:defwindow('myopathy')) is increased by high levels of HMG-CoA [reductase](javascript:defwindow('reductase')) [inhibitory](javascript:defwindow('inhibitory')) [activity](javascript:defwindow('activity')) in plasma. Laboratory abnormalities may include elevated bilirubin, alkaline phosphatase, [thyroid](javascript:defwindow('thyroid')) function abnormalities.

Marked persistent increases of [serum](javascript:defwindow('serum')) transaminases have been noted. About 5% of patients had elevations of CK levels of 3 or more times the normal [value](javascript:defwindow('value')) on one or more occasions. This was attributable to the noncardiac fraction of CK. Muscle [pain](javascript:defwindow('pain')) or [dysfunction](javascript:defwindow('dysfunction')) usually was not reported.

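### The SAE definition exempts admissions for undefined MS problems as well as relapse, so an open-label attribution can take an admission out of the 24-hour report and the by-group SAE count

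*Protocol*

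**What the plan says.** Section 8.5.5 of the protocol (Serious adverse events) makes inpatient hospitalisation one of several seriousness criteria. It takes two kinds of admission out of that criterion: those planned in advance, and "hospitalisation due to relapse or other medical problems of multiple sclerosis". Relapse has a three-part definition in 7.2.6 and a reporting step at the unscheduled visit in 10.2.4. The remainder of the phrase has no definition, list or limit anywhere in the protocol.

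Five other provisions bear on how the exemption works:

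- 8.5.5, reporting: "The investigator must submit a complete SAE report for all SAEs, regardless of a possible causal relationship". The report goes to the CRO within 24 hours.
- 8.5.1, who decides: the assessment of seriousness "of the event will be made by the investigator, who is to complete a special form provided by the sponsor".
- 7.2.4, blinding: "All patients and the treating physician will be aware whether Atorvastatin is added to the Interferon-beta-1b therapy or not". Of the treating physician it adds that "he/she will be responsible for patient eligibility, for treatment of adverse events, and for safety examinations".
- 8.5.6, expected atorvastatin reactions: these include "or cramps, blurred vision", dizziness, and "easy bruising or bleeding, itching, muscle pain or cramps, rash, and yellowing of the skin or eyes". Fatigue is listed too, as is myopathy that shows itself as muscle pain, tenderness or weakness.
- 11.1.6, output: serious events, and patients with them, are counted by treatment group.

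**The concern.** Whether an admission is an SAE depends on whether someone puts it down to MS. For relapse that is a decision against written criteria. For the open-ended remainder it is a free judgement, made in a trial where those responsible for safety know who takes atorvastatin. Several listed atorvastatin effects (weakness, dizziness, blurred vision) are also what an MS patient may present with. An admission of that kind that fails the relapse definition can be filed in good faith as an MS problem, and then neither the 24-hour report nor the SAE table will contain it.

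There is a second route. If the add-on made MS complications worse, those admissions would be exempt even when correctly attributed to MS. Safety and tolerability of the combination are a stated objective (section 6), so the comparison of SAEs between groups should not rest on an undefined, unblinded filter.

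**Working it through.** The protocol gives no figure tied to this definition, so there is nothing of its own to reproduce. The check is of the text, followed by a calculation of scale.

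**1. Is the residual category empty?** No. Under 7.2.6 a relapse needs, among other things, no fever or known infection and an objective impairment shown by the EDSS. Fatigue alone does not qualify. An admission can therefore be attributed to MS without being a relapse, and nothing bounds what falls into that gap.

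**2. Who applies it?** 8.5.1 names the investigator. Among the site roles in 4.1, the evaluating physician is kept away from safety matters by 7.2.4, and the MRI investigator has only a restricted reporting role (15.1.3). That leaves the treating physician, who is unblinded. This is an inference from the assigned roles. The protocol describes no blinded review of the attribution.

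**3. What does an exempted admission lose?** It is not an SAE, so the 24-hour rule does not reach it and it drops out of the SAE counts in 11.1.6.

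**4. What does it keep?** 8.5.5 requires all AEs to be documented. 8.5.1 requires onset, intensity, study-drug action, treatment, drug relationship and outcome. 11.1.6 tabulates AEs by preferred term and worst intensity. Hospitalisation is not among the items listed in 8.5.1, so the event would appear as a non-serious AE and the admission might not be identifiable. The CRF is not shown and may collect it.

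**5. How wide is the exemption?** It qualifies initial hospitalisation only. Death, threat to life, prolonged hospitalisation, lasting disability and the clause on other important medical events apply without any MS exception.

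**6. Scale.** Inputs: about 60 patients, half on atorvastatin (section 7), so n = 30; myopathy 0.1–0.5% (section 5).

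- One reclassified patient: 1/30 = 3.3 percentage points.
- Exact two-sided 95% limits: 0/30 gives an upper limit of 1 − 0.025^(1/30) = 11.6%; 1/30 gives 0.1% to 17.2%; 2/30 gives 0.8% to 22.1%.
- Chance of at least one event in 30, 1 − (1 − p)^30, for assumed risks p:

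| p | Chance of at least one |
| --- | --- |
| 0.5% | 14% |
| 1% | 26% |
| 3% | 60% |
| 5% | 79% |

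- Expected myopathy cases: 30 × 0.001 = 0.03 to 30 × 0.005 = 0.15.

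Serious events of any one kind will be few or absent, so one or two exempted admissions could be the whole SAE signal. The documents give no hospitalisation rate, so the number of admissions the exemption would remove cannot be estimated.

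**The case against.** The strongest reply is that little is really lost. The event stays in the AE record with its intensity and drug relationship, and a severe case of rhabdomyolysis would probably qualify under another criterion. Read literally, myopathy is not an MS problem, so it escapes only if misdiagnosed. CPK is measured in everyone at baseline, month 6 and month 12, with isoenzymes when total CPK is raised. The expected number of myopathy cases is far below one, and the patients on atorvastatin have already taken it for 12 months.

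Most of this stands and sets the limits of the point. It does not remove it. Scheduled CPK tests are six months apart, and the additional test in 8.6 is triggered by an event judged due to a study drug, so it depends on the same attribution. The myopathy figure shows how much a single case would weigh, not that one is to be expected. Nor does the reply touch admissions for MS complications that the add-on may have worsened.

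A reader might infer three stronger things that the documents do not support:

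- That exempted events have no other route of capture. They do, as AEs.
- That the exemption contradicts the duty to report whatever the causal relationship. That wording concerns causality of the study drug; leaving disease-related admissions out of the definition does not conflict with it.
- That the exception in 8.3.7 for physical findings ("except neurological findings related to multiple sclerosis") widens the gap. It governs what the treating physician reports from the physical examination. Neurological findings go to the evaluating physician under 8.3.3, and the rule is not part of the SAE definition.

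**Conclusion.** The point holds in a limited form. An undefined exemption, applied without blinding, lets an admission attributed to MS leave expedited reporting and the SAE comparison when initial hospitalisation is its only serious feature. Each such patient in the atorvastatin group shifts that group's SAE proportion by 3.3 points, assuming 30 patients. The conclusion also assumes that the treating physician makes or informs the seriousness judgement. It does not say that misattribution is likely or intended, that statin harm is exempted by design, or that any efficacy analysis is affected. It is a cheap improvement to safety reporting and to freedom from bias.

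**What to change.** - **8.5.5:** in the hospitalisation criterion, delete the words that follow relapse. Restrict the exemption to admission for an event that meets the definition in 7.2.6 and is recorded as a relapse. The exception for pre-planned admissions can stay.
- **8.5.5 and 8.5.4:** report every other unplanned admission as an SAE, including those thought to be due to MS, and put the opinion on drug relationship in the existing field.
- **11.1.6:** add a table of all hospitalisations by treatment group, whatever their attribution. If the CRF does not already record admission, add a yes/no item to the AE page.

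The cost is a short amendment, one table and a few more SAE forms in about 60 patients over 12 months. The downside is that some of the extra reports will prove to be MS-related.
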